#### Process evaluation

We will evaluate whether the intervention was delivered and received as intended (implementation). This will be achieved through completion of intervention checklists by Life Cycle UK instructors and through semi-structured interviews with instructors and participants in the intervention group at the end of the intervention. Intervention intensity, recorded by instructors, will be determined through recording of the number of intervention sessions attended by participants as well as the volume of email and telephone contact between instructors and participants. To explore the mechanisms of impact, semi-structured interviews will be conducted with participants in the intervention group to identify barriers and enablers to engaging in e-cycling. These interviews will help to identify how the intervention impacts behaviour and to determine contextual factors that may influence the intervention.

#### Assessment of harm

Participants will be asked to report adverse events resulting from e-cycling (e.g., musculoskeletal problems, falls or road traffic accidents) by calling the study phone line. The number and types of adverse events will be reported. Adverse events that mean the participant is unable to continue with the intervention will also be documented under retention rates. Qualitative interviews will be used to explore any unintended consequences that arise from participation in the study.

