As such, the *primary* aim of this study is to test the feasibility of conducting a randomized e-cycling intervention among individuals with T2DM. In order to address this aim the primary objectives are to (1) identify effective methods of recruiting individuals with T2DM; (2) determine participants’ willingness to be randomized, study retention rates, adherence to the intervention and data collection methods and harmful outcomes; (3) assess intervention fidelity; (4) qualitatively examine the acceptability of the intervention and study procedures to participants and instructors; and (5) qualitatively examine participants experiences of e-cycling. The *secondary* aim is to examine the association between the intervention and outcome measures to determine intervention promise. Accordingly, the secondary objective is to collect data on a range of individual health and behaviour outcomes in order to estimate the potential effect of the intervention (based on condition allocation) to inform outcome selection in future trials.

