#### Control group

Individuals randomly assigned to the waitlist control after baseline data collection (T0) will receive two phone calls from the researcher at approximately week 4 and 8 in order to maintain engagement in the study. During these phone calls, the researcher will direct participants to diabetes support groups and additional diabetes services being offered in the local community, in line with standard-care procedures. After post-intervention data collection (T1) these individuals will be offered training session 1 and loaned an e-bike for 3 months. Sessions 2, 3 and 4 will not be conducted. Participants will be asked to report any contact they have with other individuals in the study to ensure no contamination between conditions has occurred.

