### Measures

#### Feasibility and acceptability

The following information will be recorded to assess the feasibility of recruitment through GP practices: the number of GP practices approached, the number of practices that agree to participate as participant identification sites, the number of individuals identified through database searches and the response rates. In addition, information on the number of individuals that attend diabetes education days and the Bristol Diabetes UK support group will be recorded. Recruitment rates from the three recruitment settings, consent rates and willingness to be randomized will also be recorded. Retention rates will be determined based on the number of individuals that complete the intervention and follow-up measures. Adherence rates to study procedures will be recorded. The acceptability of the intervention and data collection methodology will be explored through semi-structured one-to-one interviews with instructors and all study participants. These interviews will be conducted by a member of the research team. Interview questions for instructors will focus on factors that impact intervention delivery, including intervention content, facilities, time and burden. Interview questions for participants will focus on thoughts and feelings regarding participation in the intervention and data collection processes. The project team will track the costs and resources required in preparation for running the intervention. Life Cycle UK will track the staff costing of intervention delivery and from the maintenance service.

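### Participants are asked to phone in only events they attribute to e-cycling, which is narrower than the harms outcome named in the primary objectives and gives no background rate from controls

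*Protocol article*

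**What the plan says.** The aims at the end of the Background make harms part of primary objective 2, which is to determine, among other things, "study retention rates, adherence to the intervention and data collection methods and harmful outcomes". Table 2 turns this into a count of harmful events, taken from study records and summarised as frequencies and percentages. Neither place limits harms to a particular cause.

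Assessment of harm sets out how events are reported: "Participants will be asked to report adverse events resulting from e-cycling", with musculoskeletal problems, falls and road accidents as examples, and they do so "by calling the study phone line". The number and types of events are then reported. Two further sentences follow. One concerns discontinuation: "Adverse events that mean the participant is unable to continue with the intervention will also be documented under retention rates". The other concerns interviews: "Qualitative interviews will be used to explore any unintended consequences that arise from participation in the study". Under Feasibility and acceptability, the acceptability interviews are described as "semi-structured one-to-one interviews with instructors and all study participants".

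Under Control group, the waitlist arm is offered the e-bike loan only after T1 data collection. Before that, controls "will receive two phone calls from the researcher at approximately week 4 and 8". The stated purpose of these calls is to keep participants engaged and to point them to local services; asking about adverse events is not mentioned.

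**The concern.** The objective and Table 2 name harms in general. The reporting instruction asks participants for one kind of harm, self-attributed, through a call they must initiate. When the instruction is narrower than the outcome, the count does not measure what the objective names.

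Two things are at stake for a pilot. The first is interpretation. Falls and musculoskeletal problems occur in inactive adults with type 2 diabetes whether or not they cycle, and without the same enquiry in controls there is no background against which to read the intervention-arm figure. The second is tolerability of the assessments. Objective 2 also covers adherence to the data collection methods, and the test battery is demanding, so events it provokes are part of what a feasibility study should learn.

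**Working it through.** The protocol gives no expected event rate, harms threshold or precision target, so there is no figure to reproduce. The check compares sections.

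**Inputs**
- Scope of the outcome: all harmful outcomes (Background, objective 2); a count of harmful events (Table 2).
- Scope of the request to participants: events attributed to e-cycling (Assessment of harm).
- Route: a call made by the participant (Assessment of harm).
- Exposure of controls before T1: no study e-bike (Control group).
- Procedures in both arms at T0 and T1: a maximal ramp test followed 20 minutes later by a supramaximal test (Cardiorespiratory fitness); cannulation and an oral glucose tolerance test with repeated blood draws (Biochemical variables).
- Arm sizes: 20 and 20 (Allocation and randomization).

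**Step 1: apply the instruction to typical events**
- A fall from the e-bike, intervention arm: within the request, and counted if the participant phones.
- Knee pain in an intervention participant who does not link it to cycling: outside the request, so by this route the team never gets to judge the cause.
- The same knee pain in a control: outside the request.
- An injury or faint caused by the exercise tests or blood sampling, either arm: outside the request. Staff may see it on the day; if it develops after the visit, nothing in the instruction asks the participant to report it.

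**Step 2: share of the sample affected**
Controls make up 20/40 = 50% of those randomised. Unless a control rides an e-bike obtained elsewhere, that half cannot have a reportable event before T1. Its count is about zero because of the definition, whatever its true rate of falls or musculoskeletal problems.

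**Step 3: can the other channels complete the count?**
- Retention record: it covers events that stop someone continuing the intervention. Controls have no intervention to stop before T1, and events that do not lead to stopping are not covered.
- Interviews: they are not limited to e-cycling, and the acceptability interviews include both arms. The process evaluation interviews are with the intervention group only. In Table 2 the interviews fall at T1 and are analysed thematically. No section says that an event mentioned there is added to the count.

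**Step 4: direction of the error**
Both filters, attribution and the need to call, can only remove events. The count is therefore likely to be too low. The size of the shortfall would need the true event rate and the proportion phoned in, and the protocol gives neither.

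**The case against.** The strongest reply is that the phone line is not the only safeguard. The interviews cover unintended consequences of taking part, reach all participants and ask about data collection, and events that end the intervention are logged under retention. A reader might infer that harms are captured only by phone; the documents do not support that. What stands is that the interviews have no stated link to the count.

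A reader might also infer that test-related events are missed. That too goes further than the text. Staff run the tests, Table 2 draws on study records without a restriction to e-cycling, and recording at visits is commonly left to a fuller protocol that is not shown. The criticism is confined to what participants are asked to report.

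A third inference is that the trial promises a comparison of harms between arms and cannot deliver it. The Quantitative analysis section says that adverse events will be described; the following sentence on descriptive comparisons may refer to sample characteristics alone. No such comparison is clearly promised.

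Nor do the documents tie harms to the size of a definitive trial: the Sample size section is about estimating a standard deviation, and none of the five progression criteria uses harms. The sentence in Quantitative analysis that names the primary outcomes does not list harms either, although objective 2 does.

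Finally, the week 4 and week 8 contacts differ between arms. Controls are called by a researcher, while intervention participants meet an instructor and are later telephoned by one. This is a fair practical objection, and the fix below allows for it.

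**Conclusion.** The point holds as a mismatch between a stated rule and a stated outcome. The only route described for participants to report countable harms is a self-initiated call about events they put down to e-cycling, whereas the objective and Table 2 are unrestricted. Followed as written, it makes the contribution of half the sample close to zero by construction, places procedure-related events outside what participants are asked to report, and is likely to understate harm.

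This assumes that no unshown document widens the request and that controls rarely use an e-bike before T1. No numerical bias is claimed. A confidence limit around a low count would reflect 20 participants per arm and not the way events are collected, so it would not measure this defect. No progression criterion depends on the count, so the consequence is a harms result that is hard to interpret; the pilot's other conclusions are not affected. It merits correction because harms sit in a primary objective and the remedy is cheap.

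**What to change.** Amend Assessment of harm as follows.

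1. Define an adverse event irrespective of its perceived cause.
2. Ask about events with the same short set of questions in both arms at the existing week 4, week 8 and T1 contacts, and record any event at the T0 and T1 test visits.
3. Keep the phone line as an additional route.
4. Judge relatedness to e-cycling or to study procedures afterwards, as a separate step.
5. State whether events raised in interviews are counted.
6. Report, descriptively and by arm, the number of events and the number of participants with at least one.

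Because instructors make the interim contacts in one arm and researchers in the other, the research team's enquiry at T1 should be the common basis for the by-arm description. The interim enquiries then mainly help recall.

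The cost is a short form, a brief added task at existing contacts (including some guidance for instructors, whose described training covers behavioural content and the manual), and a minor amendment. More minor events will be recorded. No extra visits or staff are needed.

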#### Outcome measures

Clinical outcomes are those deemed to be of importance to clinicians in the treatment of T2DM. These outcomes will be assessed at baseline (T0) and immediately post-intervention (T1) and include the following:

*Anthropometrics*. Body weight will be assessed to the nearest 0.1 kg using digital scales (TANITA Corp, Tokyo, Japan) and height will be assessed to the nearest 0.1 cm (SECA, 700 SECA, Hamburg, Germany). These measures will be used to calculate BMI (kg/m^2^). Waist circumference will be measured using a non-stretch tape measure to the nearest 0.1 cm, based on World Health Organization guidelines [38].

*Biochemical variables*. Baseline blood samples will be obtained by cannulation of the antecubital fossa from individuals in a fasted state (≥ 8 h overnight fast) to measure glucose, insulin, glycated haemoglobin (HbA1c), lipids (total cholesterol, high-density lipoprotein cholesterol, low-density lipoprotein cholesterol and triglycerides) and C-reactive protein. A total of 8 mL of blood will be taken at this time. After baseline blood samples participants will complete an oral glucose tolerance test (OGTT) which will involve consuming 113 mL of Polycal (Nutricia Advanced Medical Nutrition, Trowbridge, UK) and 87 mL of water, equivalent to 75 g of anhydrous glucose, within 5-min. Further 7 mL blood samples will be drawn at 15-, 30-, 45-, 60-, 90-, and 120-min intervals. The first 5 mL of each draw will be discarded and 2 mL of blood taken for the analysis of glucose and insulin. The intravenous cannula will be kept patent through flushing with 5 mL 0.9% NaCI (B. Braun, Sheffield, UK). All blood samples will be transported immediately to the Bristol Royal Infirmary commercial laboratory and stored at − 80 °C until analysed. Samples will be analysed individually as soon as possible after delivery. Glucose, insulin, lipids and C-reactive protein will be analysed using a Roche Cobas C701 analyzer (Roche Diagnostics, Rotkreuz, Switzerland) and HbA1c will analysed using affinity chromatography. Basal insulin and glucose values will be used to calculate insulin resistance and beta-cell function using the Homeostasis Model Assessment calculator (University of Oxford, Diabetes, Trial Unit). Using values from the OGTT, incremental area under the curve (iAUC) for insulin and glucose will be calculated using the trapezoid rule. Glucose and insulin concentrations during the OGTT will be used to estimate insulin sensitivity using the Matsuda index [39]. The insulinogenic index and oral glucose disposition index will be used to assess beta-cell function. Once samples have been analysed, the remainder of the aliquot will be destroyed by the commercial testing laboratory. Once the study is complete, any remaining samples will be disposed of in accordance with the Human Tissue Authority’s Code of Practice.

*Health-related quality of life*. The Short Form 36 Health Survey (SF-36 [40]) is a 36-item inventory designed to assess health-related quality of life (HRQL) from which 2 measures are derived, a physical component summary and a mental component summary. The physical component summary represents the average of the scales: physical functioning, role limitations due to physical health, bodily pain, and general health subscales. The mental component summary score is the average of the scales which assess energy/fatigue, social functioning, role limitations due to emotional health, and emotional wellbeing subscales. Summary scores are reported in a range from 0 to 100, with a lower score indicating lower quality of life.

Physiological outcomes will be assessed at baseline (T0) and immediately post-intervention (T1) and include the following:

*Cardiorespiratory fitness* will be determined by measuring maximum oxygen uptake (VO_2max_) using a continuous incremental ramp maximal exercise test on an electronically braked cycle ergometer (Lode Excalibur, The Netherlands). The test will start with a 4-min warm-up at 30 W, with participants cycling at a cadence of approximately 60 revolutions per minute (rpm). Following the warm up, the resistance will increase by 1 W every 4 s (15 W per minute). The test will be terminated upon volitional exhaustion or when cadence falls below 50 rpm. Expired gas will be collected continuously by a metabolic cart (Parvomedics TrueOne 2400, Salt Lake City, UT, USA). VO_2max_ is defined as the highest 15-s moving average for VO_2_ (in absolute [l/min] and relative [ml/kg/min] terms). Criteria for achieving VO_2max_ will be (1) respiratory exchange ratio > 1.15, (2) plateau in VO_2_, (3) reaching age-predicted HR_peak_ (220-age); and/or (4) volitional exhaustion. Heart rate will be monitored using a Polar chest strap, which is integrated with the metabolic cart and cycle ergometer software (Lode Exercise Manager). HR_peak_ and peak power output (*W*_peak_) will be recorded as the highest values attained in the test. Twenty minutes after completing the incremental VO_2max_ assessment, participants will complete a supramaximal test to confirm the findings of the incremental assessment. This assessment will follow guidelines outlined by Schaun [41]. The multistage test will consist of a 2-min warm-up at 30 W followed by 1 min at 60% of the incremental VO_2max_ then 110% of incremental VO_2max_ until volitional exhaustion or when cadence falls below 50 rpm [42]. The criteria for achieving VO_2max_ are the same as those reported above. Differences of ≤3% will be considered to demonstrate validation of the incremental VO_2max_ result. The higher of these two values will be taken as VO_2max._

*Body composition*. Dual-energy x-ray absorptiometry (Discovery-A; Hologic, Bedford, UK) scans will be used to assess whole-body and regional fat and lean mass using the manufacturers software. Peripheral quantitative computer tomography (pQCT; XCT 3000 scanner; Stratec, Medizintechnik GmbH, Pforzheim, Germany) will be used to assess intermuscular adipose tissue, muscle density and muscle cross-sectional area (MCSA) of the femur at 33% of the limb length. Data from the pQCT will be analysed using BoneJ [43], a freely available plugin for the software ImageJ2 [44]. Calibrations of these machines will be performed daily following manufacturers guidelines.

#### Behavioural outcomes

*Physical activity* will be measured at baseline (T0) and in the final week of the e-bike intervention. Participants physical activity will be assessed for 7 continuous days using an Actigraph accelerometer (GT3X, Actigraph, Florida, USA). The Actigraph accelerometer will be worn on an elasticated belt around the waist and taken off when sleeping, bathing or swimming. The accelerometer will record raw acceleration data at a sampling frequency of 30 Hz. Raw acceleration data will be processed using Actilife 6 software to reintegrate the data to 10-s epochs. Kinesoft software will be used to generate outcome variables describing physical activity intensity using equations developed by Freedson and colleagues [45], and the frequency and duration of physical activity. In the current study, the Actigraph accelerometer will be used to estimate total time spent in moderate-to-vigorous physical activity (MVPA) before and while having access to an e-bike. This measure has been extensively validated in both laboratory and free-living conditions [46] and has been reported to have a high completion rate in observational studies [47].

*Travel behaviour* will be measured at baseline (T0) and in the final week of the intervention, at the same time as physical activity monitoring. Spatial location will be recorded every 5 s using a personal GPS receiver (QStarz International Co. Ltd., Taiwan). Participants will be asked to wear the GPS receiver during waking hours and recharge the device at night. The device can be worn on the waist or in a pocket as desired. GPS data, in combination with accelerometer data, will be used to estimate (a) the modes of transport used by participants and (b) the amount of time spent in MVPA attributable to e-cycling and other modes of active transport.

Raw GPS data will be downloaded using Qtravel software (Qstarz International Co. Ltd. Taiwan) and extracted as csv files. Raw Actigraph acceleration data will be extracted as csv files using ActiLife 6 software (Actigraph, FL, USA). Data from these devices will be merged by timestamp using an open-source tool, which will (1) classify different modes of transportation and (2) determine the amount of MVPA attributable to different active transport modes in the merged data [48]. This tool has been found to accurately identify active travel 94.6% of the time in a cross-validation study. However, the tool has not been validated with e-cycling. As such, participants will be asked to wear a combined movement sensor and heart rate monitor (Actiheart®, CamNtech, Cambridge, UK) for the same time period as wearing the Actigraph monitor and GPS device. The Actiheart is a waterproof device worn on the left side of the chest and is attached with standard ECG electrodes. Accelerometer and heart rate data will be recorded at 15-s epochs (the shortest epoch available). Fifteen-second acceleration and heart rate data from the Actiheart device will be downloaded using Actiheart 4 software and merged with the GPS data. These data will be imported into ArcGIS for visual inspection and heart rate data will be used to confirm (or otherwise) identification of e-cycling. Once e-bike journeys have been identified, this will enable the estimation of physical activity associated with e-cycling.

#### Trip purpose

In addition to wearing a personal GPS, participants will be asked to complete a 7-day travel diary for the same time period. The travel diary will be adapted from Neves and Brand [49]. Specifically, participants will be asked to record the purpose of the trip, travel mode, the start and end time and the start and end location of each trip. Participants will be asked to classify their trip under one of eight categories: commuting, business, education, escort, shopping, visiting friends, entertainment, and recreation. For each journey, participants will be asked to report the travel mode, walking, cycling, e-biking, bus, train, car (as driver) and car (as passenger). This diary will be used to identify the purpose of trips being made by different transport modes and specifically the purpose of e-bike use.

